**3.17.1 Normality Tests**

Normality tests will be performed for age, CVD knowledge, motivation, behavioral skills, physical activity, body weight, height, BMI, diastolic, and systolic BP. Because sample size will be more than 300, histogram and total values of not more than 2 in the case of skewness and 7 on kurtosis (Kim, 2013) and also not more than a total value of 1 (Tabachnick & Fidell, 2007), will be used to determine the requirements of this assumption.

**3.17.2 Descriptive Statistics**

For descriptive statistics, means and standard deviations will be used as measure of central and dispersion to summarize continuous variables. Frequencies and percentages will be used to summarize categorical variables.

**3.17.3 Inferential Statistics**

Chi-square tests will be performed to compare baseline characteristics of groups by their socio-demographic factors, family factors, CVD knowledge, motivation, behavioral skills, physical activity, smoking status, alcohol intake, BMI, systolic and diastolic BP. Independent t-tests will be performed to determine the between groups differences of total knowledge, motivation, behavioral skills, physical activities, dietary intake, BMI, diastolic and systolic BP. At six months post intervention, the independent and paired sample t-tests would be performed to determine the between and within group differences of variables respectively. Chi-square and the McNemar tests will also be performed on smoking status and alcohol intake at six months to determine the difference between and within groups since the variables are categorical variables.

A mixed design repeated measures analysis of variance (ANOVA) will be performed after checking that there is no substantial non-normality of residuals to determine the between and within group differences and its interactions on time differences on CVD knowledge, motivation, behavioral skills, physical activity, dietary intake, body weight, BMI, diastolic and systolic BP. Intention-to- treat (ITT) analysis will be the method that will be used to handle missing data in the analysis. Replacement of data will then be conducted for each missing variable using the multiple imputation method, following which Generalized Linear Mixed Model (GLMM) analysis will be performed to determine the overall effectiveness of the intervention study.

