**[name]**

Globally, cardiovascular disease (CVD) was responsible for 17.5 million deaths, accounting for 46.2% of non-communicable diseases (NCDs) deaths. In Ghana CVDs has been the leading cause of death since 2001. The prevalence of CVD risk factors among adolescents and adults in Ghana has been increasing. The main aim of this study is to develop, implement and evaluate the effectiveness of a behavioral modification intervention program to reduce cardiovascular disease risk factors among secondary school students in Brong Ahafo, Ghana. The study will be a single blind cluster randomized controlled trial. Baseline data will be collected from 848 students after which schools will evenly be randomized using block randomization (1:1 ratio) of two digit blocks (A and B). School-based intervention will be implemented using the Information- Motivation-Behavioral skills (IMB) model to reduce CVD risk factors over a period of six months with pre and post intervention evaluations. The intervention module will be a health education and physical activity modules in the intervention schools. The control schools will go on with their normal school curriculum and will be waitlisted for similar intervention after the study. Follow-up data using same questionnaire will be collected within two weeks after the intervention is completed. The primary outcomes are knowledge, motivation, behavioral skills, physical activity, smoking, alcohol, dietary intake, while weight, body mass index, and blood pressure were secondary outcomes. Weight, height and blood pressure will be measured using standardized equipment by trained health staff. Intention-to-treat analysis will be performed after replacing missing values using multiple imputation method. The generalized linear mixed model (GLMM) will be used to test the effect of group, time and group-time interactions after controlling for potential confounders.

The study is expected to improve knowledge, motivation, behavioral skills, physical activity, and healthy eating habits among students in the intervention group. The study is also expected to reduce weight, BMI, smoking and alcohol habits of the intervention group.

i

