**3.2 Study Design**

This study is a two arm single blind parallel cluster randomized controlled trial involving four public secondary school students that will be recruited into the study from two selected districts in Brong Ahafo region and will be guided by the CONSORT statement (Moher et al., 2010). Schools will be the unit of randomization, intervention, and analysis. Respondents in the intervention arm will receive CVD behavioral modification intervention based on the IMB model, whereas the control group will not be exposed to the intervention but will go on with their normal school curricula. Students in the control group will be wait listed and will receive the intervention program at the end of the study. Baseline measurements of CVD knowledge and its risk factors, motivation, behavioural skills, physical activity, smoking, alcohol consumption, dietary intake, body weight, height, diastolic and systolic BP will be taken for both the intervention and control groups. A post intervention assessment will then be carried out within two weeks immediately after six months to evaluate the effectiveness of the intervention.

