**3.6 Sample Size Estimation**

The minimum sample size required to test the study hypotheses was calculated using the two proportions formula (Lemeshow, Hosmer, Klar, & Lwanga, 1990). The formula gave the required number (n) for each group.

2

{√2p̌ (1 − p̌) + Z1−β√p1(1 − p1) + p2(1 − p2)}

n =

(p1 − p2)2

Parameters from different intervention studies were substituted into the formula to calculate sample size as shown in Appendix H. However, a study among students by Mohammed et al. (2016) was adopted to calculate the sample size for this study.

P1 = 0.032 (proportion of students who initiated smoking among students in the intervention group after six months intervention.

P2 = 0.088 (proportion of students who initiated smoking among students in the control group after six months.

P = proportion of all subjects receiving smoking intervention after six months ((P1 +

P2)/2).

P = (0.032 + 0.088)/2 = 0.06

With Z1-α/2 = 1.96 at 95% CI and Z1-β = 1.28, at 90% power gave a minimum sample

size (n0) of 281

Adjustments were made for estimated response rates (Aday & Cornelius, 2006) thus:

i) Adjustment for estimated response rate, where the estimated attrition rate

is 20% = 337.2

This gave a sample size of 337.2 students in each group. Cluster randomized control trials are measured by design effect given as (1+ (M-1) X ICC) = 1.085.

ICC – Intra Cluster Correlation = 0.01

M – Average Cluster Size

337.2 x 1.085 (effect size of cluster random sampling) = 365.9

This gave a sample size of 366 students per group, which was then multiplied by two since the study is in two arms. Therefore, 732 is the sample required for this study.

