**3.15.3 Confounders**

The confounders in this study are age, gender, ethnicity, monthly pocket money,

family history of obesity, parent’s education and their occupation.

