**3.17 Data Analysis**

Data collected will be collated, checked, cleaned, and analyzed using IBM Statistical Package for Social Sciences (SPSS) version 22. The data analysis will be divided into descriptive and inferential statistics. The level of significance for all the statistical tests is set at 0.05. For mean estimations, 95% confidence intervals (CI) will be computed.

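### The six-month t-tests and chi-square tests ignore baseline, and the ANOVA and GLMM use it only as a change score; adjusting for the baseline value would cost nothing and usually be more precise

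*Protocol*

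**What the plan says.** Section 3.2 of the protocol has the outcomes measured in both arms at the start: "Baseline measurements of CVD knowledge and its risk factors, motivation, behavioural skills, physical activity, smoking, alcohol consumption, dietary intake", followed by weight, height and blood pressure. Sections 3.5.2 and 3.7 place the allocation of schools after baseline data collection. Section 3.15.2 makes knowledge, motivation, behavioural skills, physical activity, smoking, alcohol and diet the primary outcomes, so each has a pre-allocation value.

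Section 3.17.3 then names the analyses:

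- Continuous outcomes at six months: "At six months post intervention, the independent and paired sample t-tests would be performed to determine the between and within group differences".
- Categorical outcomes: "Chi-square and the McNemar tests will also be performed on smoking status and alcohol intake at six months".
- A mixed-design repeated-measures ANOVA (group, time, interaction) for the continuous and dietary outcomes.
- After multiple imputation, a GLMM for the overall effectiveness of the intervention. The Abstract says that the GLMM is "used to test the effect of group, time and group-time interactions after controlling for potential confounders".

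The covariates are in 3.15.3: "The confounders in this study are age, gender, ethnicity, monthly pocket money", then family history of obesity and the parents' education and occupation. The baseline value of the outcome is not listed.

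**The concern.** A baseline value measured before randomisation can be used in three ways: ignored, subtracted, or entered as a covariate. The plan ignores it in the t-tests and chi-square tests and subtracts it in the group-by-time analyses. It nowhere enters it as a covariate, which at student level is at least as precise as either alternative.

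Two things are at stake. With two schools per arm, the arms can differ at baseline by chance, and a test on the six-month value alone reports any persisting part of that difference as intervention effect. Precision that the baseline survey has already paid for is also only partly used. In addition, group, time and their interaction are all listed for testing, and no term is named as the measure of effectiveness. The group main effect averages the difference before the intervention with the difference after it. The first is zero in expectation, so the main effect estimates half the intervention effect.

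**Working it through.** **Inputs from the protocol.** Significance level 0.05 (3.17). Stated power 90%, proportions 0.032 and 0.088, ICC 0.01 (3.6). Two schools per arm (3.7.1). 424 students per arm (3.11), so about 424 / 2 = 212 per school. The correlation rho between baseline and six months is **not given**; 0.3, 0.5 and 0.7 are assumptions.

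**The plan's own figure.** The formula in 3.6 with the stated quantiles gives {1.96·√(2·0.06·0.94) + 1.28·√(0.032·0.968 + 0.088·0.912)}² / 0.056² = 375.5, not the stated 281. With 0.84 (80% power) in place of 1.28 it gives 280.8. That discrepancy is a separate matter; here it is the reason for showing both 80% and 90% as starting powers.

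**Variance of the arm difference, student level**, relative to the six-month value alone:

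- six-month value only: 1
- group-by-time (change score): 2(1 − rho)
- baseline as covariate: 1 − rho²

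The equality of group-by-time and change score was checked on simulated data (400 students, two time points): the mixed-model interaction and the change-score difference were both 0.2109 with SE 0.1001. The six-month-only estimate was 0.373 and the adjusted one 0.291.

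**Power.** With c = 1.96 + z(starting power) and f the factor above, power = Φ(c/√f − 1.96). For rho 0.5 from 90%: c = 3.24, 3.24/√0.75 = 3.74, Φ(1.78) = 96.3%.

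| rho | start | six-month only | group-by-time | adjusted | gain over better planned test |
|---|---|---|---|---|---|
| 0.3 | 90% | 90.0 | 78.2 | 92.5 | 2.5 |
| 0.5 | 90% | 90.0 | 90.0 | 96.3 | 6.3 |
| 0.7 | 90% | 90.0 | 98.7 | 99.5 | 0.8 |
| 0.3 | 80% | 80.0 | 65.8 | 83.6 | 3.6 |
| 0.5 | 80% | 80.0 | 80.0 | 89.9 | 9.9 |
| 0.7 | 80% | 80.0 | 95.1 | 97.5 | 2.4 |

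**Group main effect.** It carries half the effect, with variance factor (1 + rho)/2. From 90%, at rho 0.5: Φ(0.5·3.24/√0.75 − 1.96) = 47%.

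**With four schools.** Per arm, the school variance is 0.01/2 = 0.005 and the student variance 0.99/424 = 0.0023. The design effect is 1 + 211·0.01 = 3.11. Effects that give 80% / 90% power without clustering then have:

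- by z-test, about 36% / 45%, rising to 45% / 56% with adjustment (variance factor 0.75, rho 0.5 at both levels);
- on school means with 2 df, about 16% / 19%, rising to 19% / 24%.

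**Chance imbalance.** The SD of the baseline arm difference is √(2·(0.005 + 0.0023)) = 0.12 outcome SDs. In simulation with correlation 0.5 at both levels, the baseline difference correlates +0.49 with the six-month difference, −0.50 with the change-score difference and about 0 with the adjusted difference.

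**Stability of school effects.** Let r be the school-level correlation, with student rho and adjustment slope 0.5. Relative to six-month only:

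- adjusted: [0.005·(1.25 − r) + 0.0023·0.75] / 0.0073
- change score: [0.005·2(1 − r) + 0.0023] / 0.0073

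At r = 0.5 these are 0.75 and 1.00, and at r = 0.8 they are 0.55 and 0.59. They are equal at r of about 0.87; above that the change score is more precise.

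**The case against.** The strongest reply is that the analysis named for overall effectiveness is the GLMM, and its group-by-time term subtracts any baseline difference. Under randomisation that is a valid, unbiased comparison. Objectives 4 and 5 (1.5.2) also ask for within-group change, which a model with two time points gives and a six-month-only model does not. The full covariate set might be settled in a statistical analysis plan.

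Much of this stands. A reader might infer that no between-arm test uses baseline. The ANOVA and GLMM do, and at rho 0.7 the change score recovers most of the gain. A reader might also infer that chi-square is the only between-arm test for smoking and alcohol, because the ANOVA list leaves them out. The GLMM text excludes no outcome, and a generalized model can take categorical ones.

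Two parts do not stand. The protocol names the tests, the model terms and the covariates, so it has fixed this choice rather than deferred it. The request for within-group change is also no obstacle: a model with both time points and equal arm means at baseline gives those changes and uses baseline fully.

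**Conclusion.** The point holds in a limited form. The six-month t-tests and chi-square tests leave chance baseline differences in the result. The group-by-time analyses remove them by subtraction, which at student level is less precise than adjustment at every rho below 1. The stated covariates omit the one variable that would put this right.

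The size is modest and depends on an unstated rho. It is tempting to quote 6 to 10 points as the power this trial gives up. The documents do not support that: the figure is for independent students at rho 0.5, exactly where the gain over the better planned test peaks. With four schools the gain on school means is roughly 3 to 5 points from a low base (rho 0.5, ICC 0.01). At rho 0.5, change scores can be more precise if the school-level correlation exceeds about 0.87. There is no gain for smoking initiation, the sizing outcome in 3.6, if it is counted only among baseline never-smokers, because their baseline status is constant. Hypothesis 4 (1.6) concerns smoking prevalence, where baseline status does vary.

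The protocol nowhere says that the group main effect measures effectiveness. The point is only that it should rule this out.

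**What to change.** In 3.17.3, make the between-arm estimate for each outcome the six-month arm difference from the GLMM, in one of two forms:

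- the student's own baseline value as a covariate (baseline status for smoking and alcohol); or
- both time points kept, with arm means constrained to be equal at baseline. Allocation after baseline justifies this, and it also gives the within-group changes that the objectives ask for.

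Keep a school effect and the confounders already listed. Add the baseline value of the outcome to 3.15.3. Label the unadjusted six-month t-tests and chi-square tests descriptive. State that the group main effect is not the measure of effectiveness.

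The cost is analysis wording only, since the values are already collected. One small downside is that students with a missing baseline value rely on the planned multiple imputation.

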**3.17.4 Effect Size**

The two measures of effect size that will be used in this study are the partial eta squared and the coefficient of fixed effect. Partial eta squared, which is the proportion of the total variance in a dependent variable which is due to the intervention, will be utilized in the mixed design repeated measures ANOVA analysis. Its classification is based on small (0.01), medium (0.06) and large (0.14) (Cohen, 1988). The magnitude, also referred to as coefficient of fixed effects will be used in the GLMM analysis.

**3.17.5 Sensitivity Analysis**

Sensitivity analysis will be performed to determine the effect of drop outs in the study. The GLMM analysis will be performed and this time without replacing the missing values. The percentage differences between the coefficients will be obtained after replacement of missing data will then be calculated.

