**3.11 Intervention**

At this stage permissions and consent would had been sought from the Ministry of Education, District Directors of Education, Chairmen of the Parent Teacher Associations, parents/guardians, and students to carry out the study. All materials for the study will be ready at this stage. The objectives of the study and the eligibility criteria to participate in this study will be explained to all the students’ involved. Students will go through medical check-up which will be carried out by the two clinicians in order to pass eligibility criteria to be enrolled into the study.

The self-administered questionnaire will be given to students to complete. Health staff will measure students anthropometric and blood pressure measurements. Confidentiality and anonymity will be assured at all stages of the study. The module will be implemented in the intervention schools for a period of six months but not in the control schools. Then at the end of six months the same questionnaire will be given to students in both the intervention and the control schools. Health staff who will not take part during the baseline data collection will take anthropometric and blood pressure measurements of students at post intervention study. A total of 848 students will participate in the study; intervention (424) and the control (424) schools. Contamination of the intervention will be prevented by having intervention and control schools with distances between them.

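### The planned sensitivity analysis for drop-outs cannot test drop-out that depends on the unseen outcome, so agreement with the main analysis would not show robustness

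*Protocol*

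**What the plan says.** **Main analysis.** Protocol section 3.17.3: "Replacement of data will then be conducted for each missing variable using the multiple imputation method", followed by a GLMM for the overall effect. The abstract agrees: "Intention-to-treat analysis will be performed after replacing missing values using multiple imputation method". No imputation model and no missing-data assumption is stated. Missing completely at random appears in the abbreviation list but is not used in the analysis sections.

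**Sensitivity analysis.** Section 3.17.5 fixes three things:
- Purpose: "Sensitivity analysis will be performed to determine the effect of drop outs in the study".
- Method: "The GLMM analysis will be performed and this time without replacing the missing values".
- Read-out: "The percentage differences between the coefficients will be obtained after replacement of missing data will then be calculated". No threshold is given.

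No other section plans a scenario in which drop-outs differ from similar students who stayed. Section 3.6 expects 20% attrition, and section 3.11 plans 424 students per arm.

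**The concern.** The question that drop-out raises is what happens if the students who leave would have answered differently from similar students who stay. Standard multiple imputation fills the gaps on the assumption that they would not (missing at random). A mixed model fitted to the observed records makes an assumption of the same type. Comparing the two leaves that assumption in place on both sides.

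Drop-out could plausibly differ between the arms. Intervention schools are visited three times a week for six months (section 3.14), while control schools follow their normal curriculum (section 3.2). Students may withdraw at any time (section 3.18). Smoking and alcohol are primary outcomes (section 3.15.2) taken from a self-administered questionnaire (section 3.12.2). If drop-out in the intervention schools is related to these behaviours, the effect would be overstated, and a small percentage difference would still read as reassurance.

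Because the protocol fixes purpose, method and read-out, this is a check that does not fit its stated purpose. It is not a detail left to an analysis plan.

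**Working it through.** The protocol gives no figure for the sensitivity analysis, so there is none to reproduce. The steps below use its planning figures.

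**Inputs from the protocol.** 424 students per arm (3.11); attrition 20% (3.6); smoking initiation 3.2% in intervention and 8.8% in control (3.6).

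**Assumptions.** The planning rates are what completers show. Control drop-outs resemble control completers. Intervention drop-outs have rate *x*.

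**1. Effect of *x* on the smoking difference.** Apparent difference: 8.8 − 3.2 = 5.6 points. True intervention rate: 0.8 × 3.2% + 0.2 × *x*.

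| *x* | True intervention rate | True difference | Odds ratio, drop-outs vs completers |
|---|---|---|---|
| 8.8% | 2.56 + 1.76 = 4.3% | 4.5 points | 2.9 |
| 20% | 2.56 + 4.00 = 6.6% | 2.2 points | 7.6 |
| 31% | 2.56 + 6.20 = 8.8% | about 0 | 13.6 |

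The odds ratios divide the odds at *x* by 0.032/0.968 = 0.0331; at 31%, 0.31/0.69 = 0.449 and 0.449/0.0331 = 13.6. The exact null point is (8.8 − 2.56)/0.2 = 31.2%. In counts, 424 × 0.088 = 37.3 smokers, of whom 339.2 × 0.032 = 10.9 are seen among completers, leaving 26.5 among 84.8 drop-outs.

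**2. Would the planned comparison show this?** Trials were simulated with no true effect, 20% drop-out that depended on the unseen outcome in the intervention arm, and random drop-out in control.

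- *Smoking, at the extreme case above.* The mean log odds ratio with full data was −0.01. It was −1.15 after multiple imputation and −1.15 without. The median percentage difference was 2.3%. A false significant result occurred in 87% and 89% of trials.
- *Continuous score, random-intercept mixed model, baseline-to-follow-up correlation 0.3 to 0.7, moderate and strong mechanisms.* Both methods returned a false effect of 0.09 to 0.29 SD. Mean coefficients differed by 0.4% to 6.3%. False significance was 37% to 96%.

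School clustering was not simulated. It matters for the rejection rates but not for how the two missing-data methods compare. The unimputed smoking analysis was a two-group log odds ratio, not a full GLMM.

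**3. The read-out.** In the same continuous simulations with harmless random drop-out in both arms, the median absolute percentage difference was 8.8% to 13.0%. Under the harmful drop-out it was 1.7% to 6.1%. The true coefficient was zero, so under random drop-out the ratio was divided by something near zero. There, the percentage difference looked worse when nothing was wrong than when the whole effect was false.

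**The case against.** **The two fits need not agree.** The protocol does not say that imputation uses the same variables as the GLMM. Simulations with a true effect of 0.30 SD, about 20% loss, correlation 0.5 and assumed mechanisms gave:
- same variables in both: 0.297 imputed, 0.298 unimputed, median difference 2.2%;
- arm omitted from the imputation model: 0.242 and 0.302, about 25%;
- intervention drop-out driven by an observed covariate used only in imputation: 0.306 and 0.414, about 36%.

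The unimputed fit may also lose records with missing covariates. This stands. A reader might infer that the check will always report agreement, or that any difference is only simulation noise. The documents do not support either, because the imputation model is unspecified. The comparison can expose a faulty imputation model, or drop-out bias that imputation corrects. It still does not test drop-out that depends on the unseen outcome.

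**The extreme case is extreme.** Erasing the smoking effect needs 31% of intervention drop-outs to smoke against 3.2% of completers, with control drop-outs unaffected. Section 1.1 cites smoking among Ghanaian students aged 11 to 17 of 2.4% in boys and 1.4% in girls. For a score with an apparent effect of 0.30 SD and 20% loss, the shift needed is 0.30/0.20 = 1.5 SD in one arm only. This also stands. The document gives no ground for saying that drop-out would create the whole effect.

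**Delta values and grids belong in an analysis plan.** True of the detail. The mismatch between the stated purpose and the method is in the protocol itself.

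**Conclusion.** The point holds in a limited form. Section 3.17.5 claims more than its comparison can deliver: it cannot test outcome-dependent drop-out, and agreement between the two fits would not show robustness to it. The primary estimate is unchanged; what fails is the only planned support for its robustness to drop-out.

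Under the stated assumptions, intervention drop-outs who smoke at the control rate would remove a fifth of the planned smoking effect (5.6 to 4.5 points). At 20% they would remove three fifths (5.6 to 2.2 points). Only at about 31% would none remain.

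The missing-at-random assumption is inferred from the methods named; the protocol does not state it. The size and direction of selective drop-out are illustrative, and nothing in the document shows that it will occur.

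**What to change.** In section 3.17.5:

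1. Keep the unimputed GLMM, described as a secondary check on the imputation and not as a test of the effect of drop-outs.
2. Add delta-adjusted multiple imputation by arm for the primary outcomes. Shift the imputed values of intervention drop-outs unfavourably, for example from 0.25 to 1 SD for scores and by odds ratios of 2, 4 and 8 for smoking and alcohol.
3. Extend the grid until the conclusion changes. On the planning figures, a grid that stops at an odds ratio of 8 would not reach a zero smoking difference (13.6), and one that stops at 1 SD would not erase a 0.30 SD score effect (1.5 SD). Significance may be lost at smaller shifts. Report the shift at which the conclusion changes and say whether it is plausible.
4. Report estimates with 95% confidence intervals for every scenario, instead of percentage differences alone.

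The cost is one paragraph in the protocol, a few extra runs on imputations already planned, and a somewhat longer report.
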